### Ethical considerations

All procedures were approved by the ethics committee of the Chamber of Physicians of Hamburg, Germany. All participants of the study are informed about the study goals, procedures, analyses and data reporting prior to participation. Only data of participants (parents and youth) who gave written consent will be used for analysis. In recording video tapes for fidelity purposes, we make sure that only trainers are visible, not programme participants. Participant data are collected pseudonymised, while data analyses and published material will be anonymised allowing no conclusions on individual study participants. All data treatment is implemented according to national data security law.

### Analysis

Socio-demographic data like age, sex, school type and net household income will be compared between intervention and control group in order to check if matching of families had been successful. Longitudinal as well as cross-sectional analyses are planned as soon as post-intervention data are available, including ITT analyses. Preferred methods to test effectiveness will be repeated measures baseline-adjusted ANCOVAs, and Mixed Models to further investigate the relationships between certain characteristics of the sample and programme effectiveness. Depending on data structure, Growth Curve Analysis or Multilevel Analyses will be used to estimate and predict subjects’ development regarding substance use and behaviour problems in the future. Correlations between programme adherence, intervention competence and outcome will be applied to test for possible relations of the three variables.

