Families are admitted to the study if they have at least one child aged 10–14 years and at least one parent that is willing and able to participate in the group programme. Families are excluded if the child has a manifest substance use disorder or displays serious behavioural problems that would interfere with the group format. Children who are currently or were in the past six months enrolled in a group programme with similar goals are also excluded. In each city, 72 families are to be recruited half of which are randomly assigned to the intervention group, while the other half constitutes the control group. Thus, we aim for a total of N = 288 participating families at baseline. This sample sizes is required
[26] for detecting at least medium effect sizes in 2-point repeated measurements (like t0-t1), given a two-sided test at alpha = 0.05 and a power of 1–beta = 0.80. It is large enough to also detect small effect sizes in 4-point repeated measurements (t0-t1-t2-t3). It already takes a worst case scenario of 33% loss-to-follow-up after randomisation into account, so N = 288 is the sample sizes needed at t0. Randomisation is conducted by first matching pairs according to the criteria of school site (location of attended school), school type (educational level), sex, age (in this order) and then allocating them randomly to one of the two groups.

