### Intervention and training

Familien stärken is the approved German adaptation of the Iowa SFP 10–14. Like SFP 10–14, it is manual-based and consists of seven weekly sessions plus another four booster sessions that are conducted 4–6 months after the seventh session ends. In each session, at least three group facilitators work with 8–12 families. Programme elements are tailored to adequately address parents, children, and the entire family, respectively. SFP 10–14 aims at reducing the risk for SUD and behavioural problems. In the first part, youth and their parents meet in parallel separate sessions. Youth modules aim at improving youth’s self-efficacy and their ability to cope with stress and peer pressure. Parent modules encourage caregivers to reflect their parenting style, to develop a more consistent form of parenting (“using love and limits”) and to express positive affect more openly. In the ensuing family sessions, dysfunctional communication patterns within the family are addressed and family cohesiveness is strengthened. Special care is taken to secure high retention rates during programme participation. After each meeting, families are invited for a complementary meal which is either served by external caterers or affiliated restaurants. Also, child care is offered for families who have smaller siblings they cannot leave at home alone. As an additional incentive, families receive a voucher worth € 15 after every session. It is up to the agencies what kind of vouchers they offer; examples are cinema or swimming baths vouchers.

Facilitators were recruited among the staff of the four cooperating agencies. Most of them have a background in social work as well as several years of working experience in the field of family and youth counselling. A total of 21 facilitators were trained by experienced master trainers from the UK (Oxford Brooks University). During this mandatory three day training in Hamburg, Germany, the entire programme was presented, introducing its key elements and providing future facilitators with the opportunity to experience programme activities as participants, but also as trainers. The first author of this paper worked as an interpreter for the master trainers.

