We developed a minimal intervention to control for assessment reactivity effects. The programme gives information about the physical and mental changes affecting teenage youth. Parents are informed how they best can react to these changes and keep a trusting relationship. Video segments are used to show typical conflict situations at home and different ways to react to them. Material for this intervention came from a brochure with information about parenting for parents of adolescents (Starke Kinder - Ein Magazin für Eltern, BZgA; http://www.bzga.org), while the video segments came from another video-based prevention programme (“Freiheit in Grenzen”,
[27]). A presentation with instructions along with video segments was sent to the cooperating agencies. At each agency, a staff member was assigned to deliver the event adhering closely to the slide show and instructions. Families allocated to the control condition are invited to a one-evening-only event, at which the two-hour programme was delivered. The event is closed with a complementary meal.

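### The named effectiveness test has no term for the 8–12-family programme groups, so it is anti-conservative if sessions make families in a group more alike

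*Protocol article*

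**What the plan says.** **Delivery.** In the protocol article, under Intervention and training, the programme "consists of seven weekly sessions plus another four booster sessions", and "In each session, at least three group facilitators work with 8–12 families". For controls, "Families allocated to the control condition are invited to a one-evening-only event, at which the two-hour programme was delivered".

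**Allocation and size.** Under Methods/Design, "In each city, 72 families are to be recruited half of which are randomly assigned to the intervention group", and "we aim for a total of N = 288 participating families at baseline". Families are first paired on school site, school type, sex and age, and then allocated at random. The unit of randomisation is therefore the family within a pair, not the group.

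**Analysis.** For the effect of the programme the article says "Preferred methods to test effectiveness will be repeated measures baseline-adjusted ANCOVAs". Mixed models are reserved for how sample characteristics relate to effectiveness. Growth-curve or multilevel models are made conditional on the structure of the data and are directed at how participants develop in future. No section names programme group, facilitator or city as a level or random effect, and the sample size paragraph contains no ICC or design effect. The safeguards under Measures against bias are baseline adjustment, drop-out analysis and ITT.

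**Process analysis.** "Correlations between programme adherence, intervention competence and outcome will be applied to test for possible relations of the three variables". Under Assessment, trainers report coverage of key activities after each session, and sessions 4 and 5 are videotaped for the competence analysis.

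**The concern.** Families who spend eleven sessions (7 + 4) with the same facilitators and peers may come out more alike than families from different groups. That correlation arises after randomisation and essentially in one arm, so neither randomisation nor baseline adjustment removes it. A repeated-measures ANCOVA accounts for the correlation between one participant's measurements, but not for the correlation between families in one group. With positive within-group correlation it understates the variance of the intervention mean. Its p-values are then too small and its intervals too narrow, and this affects the article's first research question, whether the programme works.

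The process analysis has a related problem. Adherence and competence are properties of a session and its group, so all families in a group share essentially the same value. If the correlations were computed across families with no group term, their precision would be overstated.

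**Working it through.** **Inputs from the article.** 288 families, 144 per arm; 8–12 families per group; 33% loss; two-sided alpha 0.05; power 0.80.

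**Assumptions.** ICC 0.02, 0.05 and 0.10 (none is given); 10 families per group as the midpoint; loss spread evenly over groups, giving 10 × 0.67 = 6.7; clustering in the intervention arm only.

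**1. The plan's own figure.** 4 × 72 = 288 agrees. After 33% loss, 288 × 0.67 ≈ 193 remain, about 96 per arm. The power statement cannot be reproduced uniquely, because the article claims adequacy "for detecting at least medium effect sizes in 2-point repeated measurements (like t0-t1") without a numerical effect or correlation. A plain two-group comparison at d = 0.5 needs 126 families, and 126/0.67 gives 189 at baseline. At d = 0.40 the same steps give 198 and 296, close to 288. Neither calculation contains a design effect.

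**2. Number of groups.** 144/12 = 12 and 144/8 = 18.

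**3. Variance inflation of the arm difference.** DE = 1 + (m − 1) × ICC applies to the intervention arm only, so K = (DE + 1)/2.

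**4. Actual error of the nominal 5% test.** 2 × [1 − Φ(1.96/√K)].

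| ICC | K, m = 10 | Error | K, m = 6.7 | Error |
|---|---|---|---|---|
| 0.02 | 1.090 | 6.0% | 1.057 | 5.7% |
| 0.05 | 1.225 | 7.7% | 1.143 | 6.7% |
| 0.10 | 1.450 | 10.4% | 1.285 | 8.4% |

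At ICC 0.01 and m = 10 the error is only about 5.5%. A simulated baseline-adjusted ANCOVA under the null (6000 replicates, 144 per arm) agrees with the formula:

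| ICC | 8 per group | 12 per group |
|---|---|---|
| 0 | 4.9% | 4.9% |
| 0.05 | 7.0% | 8.6% |
| 0.10 | 9.1% | 11.9% |

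**5. Detectable effect and power with 96 completers per arm, 6.7 per group.** The detectable effect at 80% power is 2.80 × √(2/96 × K).

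| ICC | Detectable d | Power for d = 0.5 |
|---|---|---|
| 0 | 0.40 | 93% |
| 0.02 | 0.42 | 92% |
| 0.05 | 0.43 | 90% |
| 0.10 | 0.46 | 86% |

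Group size and completers must match here. Keeping 10 per group with 96 completers would imply 9.6 groups, fewer than were formed, and would overstate the loss (d = 0.49 and 82% power at ICC 0.10). With groups of 12 at the start (about 8 after loss), the lowest power is about 85%.

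**6. Process correlations.** For an arm mean at m = 10, the 144 families are worth 144/DE = 122 / 99 / 76 independent families at ICC 0.02 / 0.05 / 0.10. For a predictor measured at group level, the 12–18 groups limit the degrees of freedom.

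**The case against.** The article is a condensed account. It speaks of preferred methods, and random-effect structure is often left to a full analysis plan. It also mentions mixed and multilevel models, and making the latter conditional on data structure could be meant to cover nesting. A reader might infer that the article declares families independent. It does not: independence follows only from naming an ANCOVA without a group term, and an unseen plan might add one. That limits how firmly the point can be put, but does not remove it. The article does name a method for testing effectiveness, the other models are attached to different questions, and group delivery was fixed by design, so nothing about it had to await the data.

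The size of the inflation depends on an ICC that the documents do not give. Similarity due to a shared city or school is largely balanced by the matching and does not inflate the arm difference; only excess correlation from the sessions does. Leaving the pairs out of the analysis is conservative and could cancel part of the inflation. Both points stand. The offset is unquantified, however, and cannot be relied on as a safeguard.

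Controls also share an event, so treating them as singletons is a modelling choice. With one two-hour evening the induced correlation should be small, but a sensitivity analysis is reasonable.

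**Conclusion.** The point holds conditionally. If the sessions produce any positive within-group correlation, the effectiveness test as written is anti-conservative before any offset from the unmodelled pairs. Over the assumed ICC range 0.02–0.10 the actual error is about 6.0–10.4% with 10 families per group and about 5.7–8.4% after the planned loss. The inflation is slight at the low end and material at the high end.

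Two stronger readings are not supported. A reader might infer that the sample size claim for medium effects fails. If medium is taken as the conventional d = 0.5, it does not, since power remains well above 80% with group sizes reduced in line with attrition. A reader might also infer that the process correlations have an effective sample of only 12–18. That would require an ICC of 1. Nor does the article say that these correlations will be run across 144 families as independent units; it leaves the unit open.

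**What to change.** Name as the effectiveness test a partially nested mixed model with:

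- a random programme-group effect in the intervention arm, and control families as singletons;
- baseline outcome, city, and the matched pairs or matching factors in the model;
- Kenward–Roger or Satterthwaite degrees of freedom, because there are only about 12–18 groups;
- a stated ITT rule for allocated families who never attend, placing them in their scheduled group or treating them as singletons;
- a sensitivity analysis that allows clustering by shared control event.

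Relate adherence and competence to outcome with programme group as the unit or as a random effect, and report the number of groups.

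This changes analysis wording only and needs no additional families. Group membership must be kept in the analysis data, including the scheduled group of non-attenders, which attendance records alone will not supply. The price is slightly wider intervals. At ICC 0.05 the standard error rises by about 7% with 6.7 per group (√1.143 = 1.07) and about 11% with 10 per group (√1.225 = 1.11).

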### Measures against bias

At t0, research staff members who collect data in families’ homes are unaware of the families’ study condition. For the other assessments they are informed about condition status due to practical reasons (the control group parents are paid incentives for the t1-interview). As mentioned above, families are balanced between conditions regarding school site, school type, sex and age. In statistical analyses, control measures like baseline-adjusted testing, drop-out and ITT analyses will be employed.

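### The preferred multi-visit ANCOVA does not by itself deliver the promised ITT analysis when visits are missing; the mixed model already planned would, and should be the main longitudinal effectiveness test.

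*Protocol article*

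**What the plan says.** The Analysis section assigns methods to purposes: "Preferred methods to test effectiveness will be repeated measures baseline-adjusted ANCOVAs, and Mixed Models to further investigate the relationships between certain characteristics of the sample". The sentence ends by linking those characteristics to how well the programme works. Growth-curve or multilevel models are a further option, depending on the data, for describing and predicting how substance use and behaviour problems develop.

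The same section lists ITT analyses among those planned. Measures against bias adds that "control measures like baseline-adjusted testing, drop-out and ITT analyses will be employed".

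On numbers, Methods/Design says "we aim for a total of N = 288 participating families at baseline", and of this sample size: "It already takes a worst case scenario of 33% loss-to-follow-up after randomisation into account".

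The Assessment section pays control families €50 at each assessment. Programme families are paid only at the last two, because they receive other incentives during the programme.

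**The concern.** The article makes a choice here; it does not merely leave out a detail. The method named first for effectiveness needs a complete row of visits in its classical form. The method that uses whatever visits a family has is already in the plan, but is tied to the question of which families benefit.

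Two things are at stake. First, ITT: analysing families as allocated, but only if complete, does not cover all randomised families. A drop-out analysis describes the loss without repairing the estimate. Second, bias: if families who leave the programme arm differ in earlier outcome from those who leave the control arm, completers are no longer comparable. The design makes arm-related loss plausible. Assessment payments differ by arm, and seven sessions plus four boosters are compared with one evening. A programme family that misses the unpaid t1 but attends t2 and t3 would be deleted by the multi-visit ANCOVA and kept by a mixed model.

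**Working it through.** **Numbers from the article.** Four cities × 72 families = 288, or 144 per arm. At the worst-case loss, 288 × (1 − 0.33) = 192.96, about 193 families (96 per arm), so 288 − 193 = 95 would leave a listwise multi-visit analysis. The power basis of 288 cannot be reproduced, because the article gives neither a numerical effect size nor a correlation. The point does not depend on it.

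**Is loss of numbers the problem?** For a plain two-group comparison with 96 per arm, the detectable difference at 80% power is (1.960 + 0.842) × √(2/96) = 0.40 SD, against (1.960 + 0.842) × √(2/144) = 0.33 SD with all families. Taking a medium effect as d = 0.5 (assumed), power at 96 per arm is Φ(0.5 × √(96/2) − 1.960) = Φ(1.50) = 0.93. The medium-effect aim survives, so bias is the main issue.

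**Bias under stated assumptions.** Simulation settings, none of them from the article except 144 per arm and 33%: no true effect, unit variance, correlation 0.6 between any two visits, 33% loss in each arm after t1. Programme-arm loss rises with the t1 score (higher = more problems); control-arm loss is random. A negative difference favours the programme.

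| Programme-arm logit slope | Completer bias, t3 | Completer bias, t1–t3 mean | Type I error, mean |
|---|---|---|---|
| 1.0 | -0.07 SD | -0.11 SD | about 0.22 |
| 0.5 | -0.04 SD | -0.06 SD | about 0.10 |
| 0.25 | – | -0.03 SD | about 0.065 |

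An estimate from all observed data stayed at 0.00 at t3 throughout.

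**Check by formula.** At slope 1.0 the t1 difference among completers, given t0, is -0.19 SD. The coefficient of t3 on t1 given t0 is (0.6 − 0.36)/(1 − 0.36) = 0.375. Hence t3 bias = 0.375 × (-0.19) = -0.07. The same value applies at t2, so the mean is (-0.19 − 0.07 − 0.07)/3 = -0.11. Both match the table.

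**How the t3 bias changes with the assumptions.**
- Random loss, or equal slopes in both arms: 0.00.
- Slopes 1.0 and 0.5: -0.03.
- Slope 1.0 in the programme arm only, about 15% loss: -0.03.
- Slope -1.0 in the programme arm only: +0.07, against the programme.

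**A second scenario.** Correlation was 0.5, with loss at each visit depending on the previous score in the intervention arm only and 68% and 67% complete. Completer ANCOVA gave a false effect of 0.09 SD and type I error 0.17; the likelihood model gave 0.00 and 0.05. The similar completion rates did not reveal the bias. With random loss neither method was biased, and power at d = 0.3 was 0.89 for completers against 0.95 for the likelihood model.

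**The case against.** A reader might infer that the article commits to a completer analysis and so contradicts its own ITT statement. The text does not support that. Nowhere does it say that families with a missing assessment are excluded. ITT and drop-out analyses are explicitly planned, and ANCOVA on imputed data would keep every randomised family. How missing values are handled may stand in the full protocol or analysis plan, and its absence from an article is not a fault. What remains is the stated preference: the method chosen for effectiveness needs a repair that another planned method does not.

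A reader might also take 33% as the expected loss. It is a worst case, and home visits and payments are meant to keep loss lower. The vouchers given at programme sessions may also offset the unpaid assessments.

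It is tempting to quote the bias of -0.19 SD at t1, or a 17% smaller standard error there (0.094 against 0.113), as harm from the plan. Both arise only if t1 is analysed among families who also have t3. The article foresees two-point and cross-sectional analyses. In this scenario everyone has t1, and an ordinary t0–t1 ANCOVA on all of them gives about zero bias (-0.003, standard error 0.093). At t3 the precision of the two approaches is practically equal (0.114 against 0.113).

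Finally, nothing in the article shows that loss will be informative in one arm only, or in which direction. That stands, and limits the point to a risk. Growth-curve and multilevel models would normally use all observed visits too, but they are conditional and are not named as the effectiveness test.

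**Conclusion.** The point holds as a poor match between the preferred method and the ITT aim, and the wording should be changed. At the worst-case loss, a classical t1–t3 ANCOVA would rest on about 193 of 288 families and would not be an ITT analysis unless missing visits were imputed.

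The size of the bias is conditional. With 33% loss linked to t1 in the programme arm only, it is about -0.04 to -0.07 SD at t3 and -0.06 to -0.11 SD for the t1–t3 mean. It is smaller with less loss or a weaker link, zero when loss is random or equally informative in both arms, and of opposite sign if the families doing better leave. Against a small effect taken as 0.2 SD (assumed), 0.07 SD is 35% and 0.11 SD is 55%. The article describes the effects on average alcohol and tobacco use in the US trial as mostly small, so bias of this order could matter. The all-data estimate is unbiased in these scenarios because loss there depends only on observed values.

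**What to change.** Name the mixed model as the main longitudinal effectiveness test: all randomised families as allocated, all observed t1–t3 values, with arm×time and baseline×time terms. For yes/no substance-use outcomes use a logistic mixed model or equivalent, since a Gaussian model does not fit them. Keep repeated-measures ANCOVA on completers as a sensitivity analysis. The two-point t0–t1 ANCOVA can stay, on every family with t1. If ANCOVA is to remain the main multi-visit test, state that missing visits will be imputed and how.

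The cost is wording and some programming, because mixed models are already planned; no extra data or families are needed. The downside is reliance on missing at random, which one delta-adjusted sensitivity analysis can probe. Families with no visit after baseline still add no outcome information, so their number should be reported by arm.
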